### Interim analyses {21b}

#### Interim analyses

Interim safety analyses by the Data Coordinating Centre and the DSMB will occur at approximately 25%, 50% and 75% of total enrolment. Safety analyses will evaluate serious AEs by treatment arm and test for differences using a Pocock spending function approach with a one-sided type I error rate of 0.025. This approach is less conservative than what will be used to test for early efficacy results because proving definitive harm of the experimental agents is not the focus of this study. Pocock stopping boundaries at the looks described correspond to *z*-scores of 2.37, 2.37 and 2.36. This contrasts with the *z*-score stopping boundaries for the Lan-DeMets spending function that mimics O’Brien-Fleming boundaries: 4.33, 2.96 and 2.36. The unblinded statistical team will prepare these reports for review by the DSMB.

#### Interim efficacy review

The Lan-DeMets spending function analogue of the O’Brien-Fleming boundaries will be used to monitor the primary endpoint as a guide for the DSMB for an overall two-sided type I error rate of 0.05. Interim efficacy analyses will be conducted after the DSMB has selected the primary efficacy endpoint at approximately 25%, 50% and 75% of total information.

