**Methods:**

This is a multi-centre, randomized, double-blind placebo-controlled superiority trial. The study investigates the efficacy of chloroquine phosphate, hydroxychloroquine sulphate and lopinavir/ritonavir added on to standard of care compared to standard of care only in patients with COVID-19 disease. The primary outcome is the clinical status of patients measured using a 7-point ordinal scale at day 15. Research participants and clinicians will be blinded to the allocated intervention. Outcome measures will be directly assessed by clinicians. Statistical analysis will be done by a team blinded to the identity and allocation of research participants. Data analysis will follow intention-to-treat methods, using R software.

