## Outcomes {12}

COVID-19 is a new disease and our understanding of it is evolving. To align this study with other international studies, the objectives, endpoints and some other aspects of the WHO’s Master Protocol [42] have been adopted as appropriate with modifications to suite the Lagos context. There are three objectives—one primary and two secondary objectives. Each objective has three sub-objectives—one for comparing chloroquine phosphate added on to standard therapy and standard therapy alone; one for comparing hydroxychloroquine sulphate added on to standard therapy and standard therapy alone; and one for comparing lopinavir/ritonavir added on to standard therapy and standard therapy alone.

A special WHO committee developed the ordinal scale that will be used in this study for the primary endpoint [43]. This study uses a combined endpoint (based on the WHO 7-point ordinal scale) of both “clinical status and mortality” at day 15. Hence, superiority can be demonstrated when either arm shows a significant effect on the variables for clinical status OR mortality by day 15. This endpoint is particularly useful in our population given the low mortality rate, and a combined endpoint would increase the study power. The secondary endpoints will enable evaluation of the effect of the trial medications on the rate of change in the clinical condition of COVID-19 patients, as well as the safety of the trial medications (Table 3).

**Table 3 Tab3:** LACTT objectives and endpoints

**Primary objectives**	**Primary endpoints**

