#### Statistical methods for analyzing the primary outcome

The primary hypothesis is that the clinical status measured by a 7-point ordinal scale for each of the investigational arms (1, 2, 3) will be different from that of the placebo arm.

Boschloo’s test will be used to evaluate this primary hypothesis in all randomized participants (intention-to-treat analysis). For each comparison of a given arm to control, only participants concurrently randomized to those two arms will be included. Statistical significance will be claimed if the two-sided *P*-value is less than the monitoring boundary allocating a total type I error rate of 0.05 across interim analyses. The Boschloo’s test is being used instead of Fisher’s exact test because the interim results, as well as results within subgroups, will have small sample sizes based on the multiple primary outcomes within the subgroups.

The ordinal scale will be used to estimate a proportional odds model. The primary hypothesis test will be based on a test of whether the common odds ratio for treatment is equal to one. Nonetheless, estimation and confidence intervals do require the model to be correct. Accordingly, we will evaluate model fit using a goodness-of-fit likelihood ratio test. A stratified hypothesis test to account for baseline severity of disease will be used.

The distribution of severity results will be summarized by treatment arm as percentages, and participants without final outcome data will be excluded from the analysis.

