#### Access to interim results and decision to terminate the trial

The unblinded statistical team will prepare the interim result reports for DSMB review and recommendations. Analyses will be presented with blinded codes for treatment arms to protect against the possibility that the DSMB report may fall into the wrong hands. A DSMB charter will further describe procedures and membership. An additional document on statistical issues related to monitoring will be provided to the DSMB prior to interim analyses. The final decision to terminate the trial or an arm of the trial based on interim findings will be made by the DSMB, chaired by an epidemiologist.

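### The interim efficacy section reopens a primary endpoint fixed elsewhere, and the outcomes section admits success on clinical status or mortality; the 5% per comparison holds only if both are read benignly

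*Protocol article*

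**What the plan says.** Three places fix one primary endpoint.

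- The abstract (Methods) states: "The primary outcome is the clinical status of patients measured using a 7-point ordinal scale at day 15".
- Table 3 lists that scale on day 15 as the only primary endpoint, with death as its seventh category.
- The section on statistical methods for the primary outcome builds the primary hypothesis on the scale and tests whether the common odds ratio equals one. Significance is judged against a "monitoring boundary allocating a total type I error rate of 0.05 across interim analyses".

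Two places depart from this.

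- Interim efficacy review applies the O'Brien-Fleming type boundaries to the primary endpoint, "as a guide for the DSMB for an overall two-sided type I error rate of 0.05", and then says: "Interim efficacy analyses will be conducted after the DSMB has selected the primary efficacy endpoint".
- Outcomes {12} describes a combined endpoint based on the ordinal scale and concludes that "superiority can be demonstrated when either arm shows a significant effect on the variables for clinical status OR mortality by day 15".

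On access to data, the Interim analyses section has the DSMB look at serious adverse events by arm at about 25%, 50% and 75% of enrolment. The section on access to interim results says: "The unblinded statistical team will prepare the interim result reports for DSMB review and recommendations". Arms appear there under codes, and the DSMB takes the final decision to stop the trial or an arm.

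**The concern.** If the endpoint is fixed, there is nothing for the DSMB to select. If the DSMB does select it, the choice lies with the one body that sees the arms compared. Coded labels do not prevent this, because a contrast between two codes is enough to steer a choice of endpoint. No section requires the selection to come before the first report by arm. Safety looks run on enrolment and efficacy looks on information. A day-15 outcome lags enrolment, so safety data by arm can reach the board before the first efficacy look.

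The sentence in Outcomes {12} raises a second question. Taken literally, it gives each arm two routes to success, while the 0.05 is divided over looks and not between clinical status and mortality.

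Group-sequential boundaries protect the error rate of one endpoint chosen independently of the data. They protect neither a choice made on comparative data nor an either/or rule. The abstract ties a State treatment guideline to a positive result, so the success criterion needs to be unambiguous.

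**Working it through.** **Inputs from the protocol.** Overall two-sided alpha 0.05; looks at 25%, 50% and 75% of information plus the final analysis; 200 per arm with about 10% loss, so 200 × 0.9 = 180 evaluable; 603 deaths in 26,484 reported Nigerian cases (Background), so 603/26,484 = 2.3%. Correlations and the scale distribution are assumptions, because the protocol gives neither.

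**1. The plan's own boundaries.** The per-side spending function is α(t) = 2 − 2Φ(z₁₋₀.₀₁₂₅/√t), which spends 0.025 in all. Recursive integration at t = 0.25, 0.50, 0.75 and 1 gives 4.33, 2.96, 2.36 and 2.01. The protocol's text is "mimics O’Brien-Fleming boundaries: 4.33, 2.96 and 2.36", so the three interim values reproduce. With one fixed endpoint, 1,000,000 simulated trials give an error of 0.0496 to 0.0504. The 5% is right for one endpoint in one comparison.

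**2. Two tests, upper limit.** For two independent tests at full size, the error is 1 − 0.95² = 0.0975. With the boundaries from step 1 and success on either endpoint, simulation gives:

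| Correlation | Error per comparison |
|---|---|
| 0 | 0.098 |
| 0.2 | 0.097 |
| 0.5 | 0.091 |
| 0.7 | 0.084 |

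**3. Two tests at this trial's mortality.** Few deaths make the mortality test conservative: 180 × 0.023 is about 4 deaths per arm. The simulation used 180 per arm, one look, 20,000 runs, a rank-sum test on the 7-point scale and Boschloo's test on death, each at 0.05. The assumed proportions for categories 1 to 6 were 60, 12, 15, 6, 2 and 2, rescaled to leave room for death.

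| Mortality | Scale alone | Death alone | Either | Correlation |
|---|---|---|---|---|
| 2.3% | 0.052 | 0.018 | 0.068 | 0.29 |
| 5% | 0.051 | 0.034 | 0.080 | 0.42 |

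The simulation standard error is about √(0.07 × 0.93/20,000) = 0.002.

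**4. Selection between two endpoints.** Suppose the endpoint with the larger |z| is picked at a given look and only that one is tested from then on, at the step 1 boundaries:

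| Picked at | Correlation 0 | Correlation 0.7 |
|---|---|---|
| 25% | 0.070 | 0.064 |
| 50% | 0.084 | 0.074 |
| 75% | 0.093 | 0.079 |
| Final | 0.086 | 0.074 |

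If the pick is made before any data by arm are seen, it is independent of the test statistics under the null and the error stays at 0.05.

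**5. After correction.** One endpoint and one test gives 0.050, as in step 1. Two tests at 0.025 each have boundaries 4.86, 3.34, 2.67 and 2.28, and an overall error of 0.050 (correlation 0) to 0.043 (correlation 0.7).

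**The case against.** The protocol does name its endpoint, three times, and names one test. The Interim efficacy review itself first speaks of monitoring the primary endpoint. A reader might infer that the success criterion is not fixed at all; the documents do not support that. One clause contradicts an endpoint stated consistently elsewhere, and a result reported on the common odds ratio would rest on the pre-specified test.

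A reader might also infer that the DSMB chooses on the basis of efficacy results. The text does not say so. It places selection before the efficacy looks, and the only data by arm that it schedules independently of that step are serious adverse events. Nor does it offer a menu of candidates: the scale on the other study days is listed in Table 3 as secondary.

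The sentence in Outcomes {12} has a harmless reading. It follows a description of one combined endpoint in which death is the worst category, so it may only mean that an effect on death also moves the scale. That is one test with no added error. The section headed as comparing mortality rates in fact tests clinical and viral status.

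These points limit the finding but do not remove it. The wording secures neither benign reading. The sentence names two alternatives, and the primary-outcome section refers to several primary outcomes and names Boschloo's test beside the proportional odds test. An unseen analysis plan does not excuse the conflict, because this is contradictory text rather than omitted detail, and the article describes itself as the full protocol ({31c}).

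**Conclusion.** The concern holds as a contradiction to be removed. Interim efficacy review reopens an endpoint that the abstract, Table 3 and the primary-outcome methods have settled, and Outcomes {12} admits a second route to success that no alpha covers. The stated 5% per comparison is correct only if the selection is made without data by arm and the either/or sentence means one test.

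The size is conditional:

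- **Two tests:** about 6.8% at the 2.3% mortality implied by the protocol's national counts and 8.0% at 5%, under the assumed scale distribution. The limit is about 9.8% for independent full-size tests.
- **Selection between two endpoints using efficacy data by arm:** about 6.4% to 9.3%, depending on look and correlation.
- **Selection before any data by arm:** no inflation.

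A reader might be tempted to quote a much larger figure by adding the three active arms. Multiplicity across arms is a separate question, would remain after this correction, and is not counted here.

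**What to change.** 1. **Interim efficacy review:** delete the clause on the DSMB selecting the endpoint. State that interim and final efficacy analyses use the 7-point scale at day 15, and that any change of endpoint is made only by people without access to data by arm.
2. **Outcomes {12}:** replace the either/or sentence with a statement that superiority of an arm is claimed only from the common odds ratio of the ordinal scale, in which death is category 7.
3. **If mortality is meant as a second route to success:** say so and split alpha, for example 0.025 each, with the boundaries in step 5 of the working.
4. **DSMB charter (not shown):** align it if it repeats the wording.

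Items 1 and 2 cost two sentences and no data or sample size. Item 3 has a price. Ignoring the looks, 85% power at 0.05 corresponds to 1.960 + 1.036 = 2.996. At 0.025 the critical value is 2.241, which leaves 2.996 − 2.241 = 0.755, so power for the ordinal scale alone falls to Φ(0.755), about 77%, at the same 200 per arm.

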#### Conditional power

Conditional power will be presented as an additional guide to the DSMB. Conditional power allows computation of the probability of obtaining a statistically significant result by the end of the trial given the data accumulated thus far, incorporating and assuming a hypothesized treatment effect (e.g. the treatment effect assumed for sample size determination) thereafter. If conditional power is less than 20% under the original trial assumptions, consideration will be given to stopping the trial.

#### Access to interim results and decision to terminate the trial

The unblinded statistical team will prepare the interim result reports for DSMB review and recommendations. Analyses will be presented with blinded codes for treatment arms to protect against the possibility that the DSMB report may fall into the wrong hands. A DSMB charter will further describe procedures and membership. An additional document on statistical issues related to monitoring will be provided to the DSMB prior to interim analyses. The final decision to terminate the trial or an arm of the trial based on interim findings will be made by the DSMB, chaired by an epidemiologist.

### Methods for additional analyses (e.g. subgroup analyses) {20b}

#### Evaluating safety and tolerability relative to the control arm

Safety will be evaluated by comparing the proportion of patients with at least one serious adverse event (SAE) for each study arm relative to the control arm, using a two-sided Fisher’s exact test at alpha = 0.05. Proportions of specific SAEs will be reported for each study arm. Clopper-Pearson confidence intervals for within-arm proportions will be presented.

We will tabulate the number (%) of patients with at least one SAE for each study arm. *P*-values comparing each arm to control using two-sided Fisher’s exact test at alpha = 0.05. The number (%) of patients with specific SAEs by System Organ Class (SOC) and Preferred Term (PT) will also be tabulated. *P*-values comparing each arm to control using two-sided Fisher’s exact tests at alpha = 0.05.

List of SAEs: randomized arm, days from randomization to first SAE experienced by a subject, subject ID, site, age, days from the start of study drug to SAE, SAE, severity grade, relatedness to study intervention, outcome (sort by randomized arm, subject ID, SOC and PT and, if a subject has multiple SAEs, days from randomization to SAE).

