## Sample size {14}

The sample size of 200 per arm has been calculated assuming an odds ratio (*OR*) of 2, 85% power and a 2-tailed test at level *α* = 0.05 and allowing for approximately 10% of participants to be lost to follow-up. The odds ratio represents the odds of improvement in the ordinal scale for treatment relative to control.

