### Comparing mortality rates of investigational arms to the control arm up to 29 days after randomization

Boschloo’s test will be used to evaluate 15-day and 29-day clinical status and SARS-CoV-2 viral status in the manner proscribed for the primary and secondary analysis.

Table: Sample size, number (%) with 15-day 7-point ordinal scale clinical outcome status, number (%) missing 15-day 7-point ordinal scale clinical outcome status and 15-day SARS-CoV-2 viral status. *P*-values from Boschloo’s test comparing each arm to control.

Table: Sample size, number (%) with 29-day 7-point ordinal scale clinical outcome status, number (%) missing 29-day 7-point ordinal scale clinical outcome status and 29-day SARS-CoV-2 viral status. *P*-values from Boschloo’s test comparing each arm to control.

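### The final SAE comparisons use Fisher's exact test without a stated reason, although Boschloo's test is already in the plan and is never less powerful; switching is a small, free improvement

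*Protocol article*

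**What the plan says.** In the protocol article, item 20b, the section on evaluating safety and tolerability relative to the control arm describes the measure as "comparing the proportion of patients with at least one serious adverse event (SAE) for each study arm relative to the control arm". For the test itself, the text specifies "using a two-sided Fisher’s exact test at alpha = 0.05". For the tables of SAEs by System Organ Class and Preferred Term, the wording is "comparing each arm to control using two-sided Fisher’s exact tests at alpha = 0.05". No reason is given for the choice of test.

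The section on the primary outcome makes the other choice. Boschloo's test is applied there to all randomized participants, and Fisher is set aside by name: "The Boschloo’s test is being used instead of Fisher’s exact test". The reason offered there is "because the interim results, as well as results within subgroups, will have small sample sizes". The section headed as a comparison of mortality rates up to day 29 continues in the same way: "Boschloo’s test will be used to evaluate 15-day and 29-day clinical status and SARS-CoV-2 viral status".

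On size, item 14 states: "The sample size of 200 per arm has been calculated assuming an odds ratio". The ratio assumed is 2, and a loss to follow-up of about 10% is built in. The study setting section (item 9) plans 200 participants at each of three centres.

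**The concern.** The plan names two exact tests for comparing an arm with control and gives the SAE comparison the more conservative one without saying why. That comparison (at least one SAE or none, arm against control) is a plain 2×2 table, which is the setting Boschloo's test was built for. Boschloo's test takes Fisher's P-value as its statistic and recalibrates it so that the unconditional size comes as near to 0.05 as it can without exceeding it. It therefore rejects whenever Fisher rejects, and sometimes when Fisher does not. What is at stake is some power to detect an excess of SAEs, given up for no gain in error control.

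**Working it through.** **Inputs**
- Test and level: two-sided Fisher, 0.05 (item 20b, safety section).
- Size: 200 per arm (item 14). With 10% loss, 200 × 0.9 = 180 evaluable. The study setting section gives 3 × 200 = 600 in total, and 600 / 4 equal arms = 150 per arm, against 4 × 200 = 800 under item 14. All three sizes are run.
- SAE rates: assumed, because the protocol states none. Control rates from 0.5% to 10% and active-arm rates from 2% to 20% were tried.

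The plan states no power for the SAE comparison, so there is no figure of its own to reproduce.

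**Method.** For n per arm, let X and Y be the SAE counts in the active and control arms, with X ~ Bin(n, p1) and Y ~ Bin(n, p0). The rejection probability is the sum of P(X = x) × P(Y = y) over all tables the test rejects. Fisher rejects when its two-sided P ≤ 0.05. Boschloo rejects when that same P ≤ c, where c is the largest cut-off that keeps the size at or below 0.05 for every common rate.

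**Size**

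| n per arm | Fisher, maximum size | Boschloo cut-off c | Boschloo, maximum size |
|---|---|---|---|
| 200 | 0.040 | 0.0572 | 0.0496 |
| 180 | 0.040 | 0.0576 | 0.0497 |
| 150 | 0.043 | 0.0616 | 0.0495 |

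Both tests fall well below 0.05 when events are rare. At 200 per arm and a common rate of 3% to 5%, Fisher's size is 0.022 to 0.029 and Boschloo's 0.026 to 0.033. At 1% both are 0.0049.

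**Power in %, Fisher → Boschloo**

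| Control v active | 200 per arm | 180 per arm | 150 per arm |
|---|---|---|---|
| 0.5% v 3% | 31.4 → 31.5 | 25.7 → 25.8 | 17.1 → 25.6 |
| 1% v 3% | 16.9 → 17.3 | 14.1 → 14.3 | 9.8 → 14.2 |
| 1% v 5% | 56.3 → 58.4 | 50.1 → 51.8 | 39.6 → 45.7 |
| 2% v 6% | 44.0 → 46.5 | 38.6 → 42.3 | 30.5 → 36.4 |
| 3% v 8% | 52.2 → 54.4 | 46.8 → 50.7 | 37.7 → 42.6 |
| 5% v 10% | 40.6 → 43.1 | 36.1 → 39.0 | 29.8 → 32.9 |
| 5% v 15% | 90.5 → 91.5 | 86.7 → 87.9 | 79.7 → 81.5 |
| 10% v 20% | 76.8 → 79.0 | 71.7 → 73.8 | 62.9 → 66.7 |

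Over all pairs tried, the gain is about 0 to 2.5 points at 200 per arm, 0 to 4 at 180, and 1.8 to 8.5 at 150.

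**Why the size per arm matters.** Take a 5 v 0 split with equal arms. Fisher's two-sided P is 2 × C(n,5) / C(2n,5).
- n = 200: 2 × 0.0305 = 0.061, above c = 0.0572. Boschloo's P is 0.051, so neither test rejects.
- n = 150: 2 × 0.0302 = 0.060, below c = 0.0616. Boschloo's P is 0.048, so only Boschloo rejects.

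At 180 and 200 per arm the smallest significant splits are the same for both tests: 6 v 0, 8 v 1 and 10 v 2. That is why the gain there is close to zero for very rare events.

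**The case against.** The case for leaving Fisher in place is respectable. It controls the type I error, is standard for SAE tables, and sits naturally beside the Clopper-Pearson intervals planned in the same section. At the stated 200 per arm the largest gain over the rates tried is 2.5 points. SAEs up to day 29 under intention to treat would ordinarily be counted over all 200 randomized, not 180. All of this stands, and it limits the point to an improvement.

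Several stronger readings are tempting, and the document does not support them.
- A reader might infer that the plan breaks its own rule, having dropped Fisher because events are few. The stated reason is small sample sizes at interim looks and in subgroups of the primary outcome. It does not reach a full-sample SAE table. What remains is that Boschloo's test is also planned for full-sample comparisons, so its use is not confined to small samples.
- A reader might infer that SAEs are the rarest events compared, or that Boschloo's test helps most where events are rarest. No SAE rate is given, and the outcomes section calls mortality low. At 180 to 200 per arm the gain shrinks as events become rarer.
- A reader might infer that harm is consistently tested less sensitively than benefit. The interim plan does the opposite: the first-look boundary is z = 2.37 for SAEs and 4.33 for efficacy. Its remark that proving definitive harm is not the focus explains that interim boundary. It is not a reason for the choice of final test.
- A reader might blame Fisher for a final test that runs well below 0.05. With rare events Boschloo's test also does.

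It can also be said that the existing use of Boschloo's test is a poor model, since it is a 2×2 test named for a seven-category scale. That is a separate matter. The SAE comparison really is 2×2.

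**Conclusion.** The point holds as a free improvement, not as an error. Fisher is valid here but conservative, and the plan already contains an exact test that is never less powerful at the same level.

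The benefit is small at the stated 200 per arm and modest at 180. It becomes material only if the trial has about 150 per arm, as the per-centre figure implies. The power figures rest on assumed SAE rates, equal arms and four open arms.

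Low power for harm comes mainly from few events: at 200 per arm, 2% against 6% has 44% power with Fisher and 46.5% with Boschloo. At 180 to 200 per arm the tables by preferred term, where counts are smallest, would gain little.

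**What to change.** In the safety section of item 20b, name a two-sided Boschloo's test at 0.05 for the comparison of patients with at least one SAE and, for consistency, in the System Organ Class and Preferred Term tables. State that the statistic is Fisher's two-sided P-value, so that the test still rejects whenever Fisher does if arm sizes end up unequal. If Fisher is preferred, one sentence giving the reason would settle the matter.

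The change is a few words, made before unblinding. The test is already planned, so it needs no new data and keeps the 0.05 level for each comparison. Reconciling 200 per arm with 200 per centre would show which of the gains above applies.
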